### **5.3 Withdrawal of individual subjects**

Not applicable.

Patient data will be anonymized, and data will be gathered as part of standard of care. Therefore patients cannot withdraw.

Although we use anonymous data, according to the UMC policy (and GDPR) we will

be excluding patients who object against the use of their data for research purposes (general 'no-object').

**5.4 Replacement of individual subjects after withdrawal**

Not applicable.

**5.5 Follow-up of subjects withdrawn from treatment**

Not applicable.

## 6. STATISTICAL ANALYSIS

Missing data are not expected as most parameters are obligatory used items in the synoptic pathology reports which are to be used.

### 6.1 Primary study parameter(s)

As the primary outcome measure is dichotomous, a simple Chi-squared test will be used to test for differences in the proportion of IHC-use in both arms. Furthermore, relative risks (of IHC-use) will be calculated.

For baseline comparisons between both arms, we will use the appropriate measures (parametric or non-parametric) for categorical (Chi-squared test/Fisher's exact) and continuous parameters (T-test, Mann-Whitney U test).

Although we do not expect differences in patient- and tumor characteristics between both groups, we will adjust for them if they are observed. We do not plan to perform the often used logistic regression model, but we will explore alternative models like Poisson regression with robust standard errors or log-binomial regression, as these will provide adjusted relative risks instead of odds ratio's provided by logistic regression.

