### **General group assignment**

SN-specimens of breast cancer patients will be assigned to be assessed by a pathologist with or without AI-assistance in a pragmatic bi-weekly sequential design. This is deemed feasible as case-mix variation and time trends have not been observed previously, and as this is highly unlikely to occur within the envisioned inclusion-period of approximately six-nine months. Furthermore, specialized breast-pathologists within the UMCU work according to (bi)weekly schedules. Therefore using AI every two weeks, as opposed to switching by day, ensures that all breast pathologists are equally distributed between groups. Lastly, it would be unworkable to switch from AI-assistance to no AI-assistance on a case to case basis.

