#### 3.4 Sample size calculation

All SN-specimens assessed within the UMC Utrecht for three consecutive months (August 1st – November 1st 2021) were analyzed. In total, 83 SN-specimens were assessed, for which in 68 cases (81.9%) IHC was performed.

In 24/83 SN-specimens metastases were detected (8 macro-metastases, 8 micro-metastases, and 8 x isolated tumor cells).

- o All 8 macro-metastases were detected without IHC
- o 2/8 micro-metastases were detected without IHC
- o None of the 8 cases with isolated tumor cells were detected without IHC

We presume that the AI-algorithm will detect all metastases for which currently IHC is used. This means that for 14 metastases (6 micro-metastases + 8 ITC) no IHC will be used in the intervention group, whereas in the control group, IHC would be used. This leads to the following proportions per arm:

- $P1 = 68/83 = 0.819$
- $P2 = (68-14)/83 = 0.651$

A one-sided test was used, as we are only interested in a one-sided outcome, i.e. less IHC being performed in the AI-assisted arm. In addition, it is not likely that more IHC will be performed in the AI-assisted arm, as in both arms pathologists make the call whether to perform IHC. So even if the AI-algorithm would not recognize any metastases, the

pathologist would still look at the HE-slide and check whether there are no metastases (morphologically), which is exactly what the pathologists in the other arm are doing.

Calculations were performed in R by using the `power.prop.test` command (see below).

```
> power.prop.test(n=NULL, p1=0.819277108, p2=0.650602409, sig.level=0.05, power=0.8, alternative = "one.sided")

Two-sample comparison of proportions power calculation

      n = 83.61041
     p1 = 0.8192771
     p2 = 0.6506024
sig.level = 0.05
  power = 0.8
alternative = one.sided

NOTE: n is number in "each" group
```

We decided to be conservative and include 90 SN-specimens (i.e. from 90 patients) per arm. This will take approximately 7 to 8 months.

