### Primary endpoint analysis

For the analysis of the primary endpoint, the proportions of IHC-use in all cases of detected SN-metastases were compared, and adjusted risks were calculated using a log-binomial regression model (1-6), with starting values provided by the simple approach suggested by Schwendinger *et al* (7, 8) and 95% confidence intervals (CI) calculated by bootstrapping (n=1,000) (1).

Potential confounders were identified a-priori during discussions with all participating pathologists. Two factors may play a role here. First how diligently a pathologist looks at the HE-section could potentially be influenced by tumor characteristics on biopsy. However, all participating pathologists stated that they virtually always look at an SN without prior looking at any of the tumor characteristics on biopsy. In this light, it is also important to mention that the SN-specimen is always assessed a day before the resection specimen of the tumor itself. Hence, many (if not all) tumor characteristics (either derived from the biopsy or the resection specimen) are unknown to the pathologist who assesses the SN-specimen. Second, some tumor characteristics may influence the visibility of metastasized cells. Two of these potential confounding factors were identified. First, the size of metastases (i.e. macro-metastases ( $\geq 2\text{mm}$ ), micro-metastases ( $< 2\text{mm}$ ) or ITC) influences their visibility to a pathologist (either with or without AI-assistance), and consequently influences the use of IHC. The same holds true for histologic subtype, as for example lobular cancer cells are known to be more difficult to identify on the HE-section.

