### Sample size calculations

Sample size calculations were based on a retrospective analysis of 83 consecutive SN-specimens from a period of three months in the UMC Utrecht. We assumed that the AI-assisted pathologist would detect all metastases without IHC for which currently IHC is needed, which are mainly micro-metastases and ITC (~15%). Of the 83 cases, IHC was used in a total of 68 cases (0.819), mainly consisting of negative cases and 14 cases of ITC and micro-metastases. We assumed that these 14 cases would be detected by the algorithm, without the need for IHC. This resulted in a presumed proportion of IHC-use in the intervention arm of 0.650 (54/83). This sample size calculation is thus built on two assumptions, being a presumed similar overall distribution of negative cases and cases of ITC, micro- and macro metastases during the trial, and a presumed proportion of IHC-use in the intervention arm based on assumptions of the accuracy of the algorithm. Therefore, the sample size calculation is in theory indirect. However, it was deemed the best way calculate clinically applicable sample sizes for this trial.

We used a one-sided significance level of 5%, as it was deemed impossible to use more IHC

after AI-assistance, and a power of 80%, resulting in a sample size of 166 SNs (83 per arm). As there are uncertainties on the assumption of the amount of metastases that the AI-assisted pathologist would detect without IHC, we decided to include 180 SNs (90 per arm) to be on the safe side.

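### Protocol 6.1 adjusts the primary IHC comparison only if imbalance is seen, the SAP adjusts without that condition, and neither makes an adjusted test primary

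*Combined protocol and SAP*

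**What the plan says.** Protocol section 6.1 states that "a simple Chi-squared test will be used to test for differences in the proportion of IHC-use in both arms", with relative risks alongside. It then plans between-arm tests of baseline characteristics and continues: "Although we do not expect differences in patient- and tumor characteristics between both groups, we will adjust for them if they are observed". Poisson or log-binomial models are to be explored for that purpose. There is no covariate list and no definition of when a difference counts as observed.

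The SAP, under 'Primary endpoint analysis', reads differently. It compares IHC-use among detected metastases and reports adjusted risks from a log-binomial model with bootstrap 95% intervals, with no 'if observed' condition. It identifies size of metastasis and histologic subtype as potential confounders. Of size it says that it "influences their visibility to a pathologist (either with or without AI-assistance), and consequently influences the use of IHC". It does not write out the model's covariates or say that the adjusted result decides the primary question. The SAP's section on comparisons between arms names only chi-squared and Fisher tests for categorical variables.

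Allocation alternates every two weeks and is not randomised. The protocol ('General group assignment') justifies this partly on the ground that "case-mix variation and time trends have not been observed previously".

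**The concern.** Without randomisation, balance between the arms has to be assumed or handled in the analysis. Section 6.1 handles it through a gate: look for differences, and adjust only if some are found. A baseline comparison in a small trial is a weak detector of imbalance. Here the key factor is very strong: in the protocol's own pilot (section 3.4), IHC was used in 0/8 macro-metastases, 6/8 micro-metastases and 8/8 cases of isolated tumour cells (ITC). If the AI fortnights happened to receive more macro-metastases, IHC-use would fall without any contribution from the algorithm, and the gate might stay shut.

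There is also a cost when nothing is out of balance. An unadjusted test leaves in the variation between size classes, which the trial records anyway and could remove.

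Because protocol and SAP give different rules, the analyst could follow either one, and a crude and an adjusted result could disagree with no stated order of precedence.

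**Working it through.** **The plan's own figure.** The pilot gives the control rate: "In total, 83 SN-specimens were assessed, for which in 68 cases (81.9%) IHC was performed". So p1 = 68/83 = 0.8193 and p2 = (68 − 14)/83 = 0.6506, with one-sided 5% and 80% power. With p̄ = 0.7349,

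n = [1.645·√(2p̄(1−p̄)) + 0.842·√(p1(1−p1) + p2(1−p2))]² / (p1−p2)² = (1.0267 + 0.5156)² / 0.1687² ≈ 83.6 per arm.

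This reproduces the protocol's 83.61. At the planned 90 per arm the power is 82.5%.

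**Inputs for the check.**
- Pilot mix: 8 macro, 8 micro, 8 ITC and 59 negative of 83.
- IHC-use by class: macro 0, micro 0.75, ITC 1, negative (68 − 14)/59 = 54/59.
- Expected positives per arm: 90 × 24/83 ≈ 26.
- Assumptions not in the documents: the size of each case-mix shift; that a difference is 'observed' when a chi-squared test on size class has p<0.05; and a size-stratified Mantel-Haenszel test standing in for any size-adjusted analysis.

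**What a shift does by itself (no AI effect).** Among positives, expected control IHC-use is (0 + 0.75 + 1)/3 = 0.583. If macro-metastases are 50% of the AI arm's positives, with the rest split equally, it is 0.5 × 0.875 = 0.4375. The spurious relative risk is 0.4375/0.583 = 0.75. Over all specimens, IHC-use outside the macro class is 68/75 = 0.907. Doubling the macro share from 8/83 to 16/83 gives (1 − 0.193) × 0.907 = 0.732 against 0.819.

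**The three rules.** Unadjusted: pooled z test of two proportions. Stratified: Z = Σ(x₁ₖ − n₁ₖtₖ/Nₖ) / √Σ[n₁ₖn₀ₖtₖ(Nₖ−tₖ)/(Nₖ²(Nₖ−1))] over size classes k. Here x₁ₖ is the AI arm's IHC count, n₁ₖ and n₀ₖ are the arm sizes, tₖ is the total IHC count and Nₖ the total number. Gated: stratified if the baseline p<0.05, otherwise unadjusted. Each rejects when Z < −1.645. There were 100,000 simulated trials per row.

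| Scenario | Baseline test flags | Unadjusted rejects | Gated rejects | Always stratified rejects |
|---|---|---|---|---|
| Positives, 26/arm, no effect, macro 33% v 33% | 5.1% | 6.2% | 5.2% | 4.7% |
| same, 50% v 33% | 17.8% | 31.8% | 18.4% | 5.1% |
| same, 60% v 33% | 40.1% | 56.7% | 22.7% | 5.3% |
| same, 67% v 33% | 58.9% | 73.1% | 21.3% | 5.8% |
| All specimens, 90/arm, no effect, macro 9.6% v 9.6% | 4.9% | 5.2% | 4.7% | 5.0% |
| same, 15% v 9.6% | 12.6% | 20.3% | 13.9% | 5.1% |
| same, 19.3% v 9.6% | 30.5% | 41.0% | 20.1% | 5.1% |
| same, 28.8% v 9.6% | 81.2% | 84.6% | 13.5% | 5.2% |
| Positives, equal mix, AI removes half of IHC need | 5.0% | 73.3% | 74.5% | 89.4% |
| All specimens, equal mix, planned effect | 4.9% | 82.9% | 83.9% | 96.3% |
| All specimens, equal mix, AI finds half | 4.9% | 39.2% | 39.4% | 54.7% |

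Testing macro yes/no instead of all classes flags somewhat more by the normal approximation: 23% for 50% v 33%, 45% for 19.3% v 9.6%, and 91% for 28.8% v 9.6%. For case mix alone to produce the whole planned reduction, the macro share would need to be 1 − 0.6506/0.9067 = 28%.

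**The case against.** The strongest reply is that the SAP already deals with this. Its primary analysis adjusts without a gate, and metastasis size, the variable behind every scenario above, is one of its two named confounders. An adjusted relative risk with a 95% interval is adjusted inference. This largely stands. A reader might infer that the trial has no protection against case-mix shift; the SAP does not support that. What the SAP leaves open is whether its analysis supersedes section 6.1, which covariates are in the model, and which result is the test.

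Second, reading 'observed' as p<0.05 is an inference. If it means a difference of at least 10 percentage points in any size class (also an assumption), the gate opens in 87% of trials for the 50% v 33% shift. False positives are then about 5%, and power among positives with AI removing half of the IHC need is 86%. So the size of the problem depends on a definition that the protocol does not give.

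Third, the shifts are hypothetical. No document reports one, the arms interleave over months, and chance imbalance from a common mix leaves the gated rule at about 5%. Nor do the figures show that a shift large enough to mimic the whole planned effect would pass unseen: it is flagged in 81-91% of trials.

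Fourth, a reader might infer that the trial is underpowered. At its own planning assumptions the unadjusted all-specimen test has 82.5% power, which meets the 80% target. The loss is only relative to an adjusted test.

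**Conclusion.** The point holds as a conflict to be reconciled, with a measurable cost if section 6.1 is the rule followed. The documents disagree on whether adjustment is conditional, the condition is undefined, and the only named tests of IHC-use are unadjusted.

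Under the p<0.05 reading, moderate systematic shifts are mostly missed and one-sided error rises to about 18% at 50% v 33%; size stratification keeps it at about 5%. The power gain does not depend on any shift. It is about 15 points among positives if AI removes half of the IHC need (74% to 89%) and about 12 points over all specimens at the planned effect (84% to 96%). Both rest on the pilot's IHC rates by size class, which come from eight cases each. The effect of histologic subtype cannot be sized, because the documents give no rates for it.

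**What to change.** - In protocol 6.1, delete the conditional adjustment sentence and report baseline data descriptively.
- In both documents, state that the primary inference on IHC-use is adjusted for metastasis size class whatever the baseline comparison shows. One route is the SAP's log-binomial model with its covariates (size, subtype) written out and the decision rule for the adjusted relative risk stated. The other is a Cochran-Mantel-Haenszel test stratified by size class, exact if sparse. The second is useful because zero or complete IHC-use in a size class, as in the pilot, can put the log-binomial model at its boundary; the SAP already cites a source on that problem.
- Keep the crude chi-squared test and crude relative risk as supportive.
- If IHC-use over all specimens is also tested, stratify by final nodal category (negative, ITC, micro, macro).
- Size class is assigned after the read and might be slightly affected by whether IHC was done. Add a sensitivity analysis with macro against micro and ITC combined.

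The cost is wording and one standard analysis on data already recorded. No extra specimens or readers are needed.

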### 6.2 Secondary study parameter(s)

Time needed to evaluate a biopsy or lymph node

Will be compared by either a (parametric) T-test or a (non-parametric) Mann-Whitney U test, when appropriate.

Satisfaction with AI-assisted work-flow (questionnaire)

A quantitative analysis will be performed.

### 6.3 Other study parameters

Number of IHC's that would not have needed to be performed after AI-implementation

In the AI-arm, the number of IHC-stainings which, based on the evaluation of the AI-assisted pathologist, could have been omitted will be determined (i.e. the sensitivity of the AI-assisted pathologist will be determined).

## **7. ETHICAL CONSIDERATIONS**

### **7.1 Regulation statement**

The study will be conducted according to 'gedragscode gezondheidsonderzoek' and in accordance with the EU GDPR (General Data Protection Regulation) and Wet Medisch Wetenschappelijk Onderzoek.

### **7.2 Recruitment and consent**

Informed consent is not required for the following reasons:

1. Standard care, i.e. assessment by a pathologist and IHC when no tumor cells are detected, is performed in all cases. Hence, there is no chance of an inferior diagnosis (missed tumor cells). Also, patients (more specifically their tissue specimens) are not subjected to any actions, nor are rules of conduct imposed on them. Therefore, overall patients just receive standard care and are at no risk. One could also think of it like performing an extra staining in routine diagnostics, for which informed consent is never required.
2. Secondly, all data will be anonymous to the researchers.

## **8. ADMINISTRATIVE ASPECTS AND PUBLICATION**

### **8.1 Handling and storage of data and documents**

Data will be anonymized to the researchers, who will access it in Castor, to ensure data security. Data will be kept for a period of 15 years. For further details please see the data management plan (DMP-Online).

### **8.2 Amendments**

Amendments are changes made to the research after an ethical committee gave an advice non-WMO. Any change that may cause the investigation to fall within the scope of the WMO is submitted to the ethical committee that gave the non-WMO advice.

## Statistical analysis plan for the CONFIDENT-B trial

### Statistical tests for comparisons between arms

For comparisons between both arms, parametric or non-parametric measures were used when appropriate for continuous (T-test, Mann-Whitney U Test) and categorical variables (Chi-squared test/Fisher's exact test).

### Primary endpoint analysis

For the analysis of the primary endpoint, the proportions of IHC-use in all cases of detected SN-metastases were compared, and adjusted risks were calculated using a log-binomial regression model (1-6), with starting values provided by the simple approach suggested by Schwendinger *et al* (7, 8) and 95% confidence intervals (CI) calculated by bootstrapping (n=1,000) (1).

Potential confounders were identified a-priori during discussions with all participating pathologists. Two factors may play a role here. First how diligently a pathologist looks at the HE-section could potentially be influenced by tumor characteristics on biopsy. However, all participating pathologists stated that they virtually always look at an SN without prior looking at any of the tumor characteristics on biopsy. In this light, it is also important to mention that the SN-specimen is always assessed a day before the resection specimen of the tumor itself. Hence, many (if not all) tumor characteristics (either derived from the biopsy or the resection specimen) are unknown to the pathologist who assesses the SN-specimen. Second, some tumor characteristics may influence the visibility of metastasized cells. Two of these potential confounding factors were identified. First, the size of metastases (i.e. macro-metastases ( $\geq 2\text{mm}$ ), micro-metastases ( $< 2\text{mm}$ ) or ITC) influences their visibility to a pathologist (either with or without AI-assistance), and consequently influences the use of IHC. The same holds true for histologic subtype, as for example lobular cancer cells are known to be more difficult to identify on the HE-section.

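### The bootstrap interval for the primary relative risk collapses to [0, 0] when no AI-arm metastasis needs IHC, which is the outcome the plan assumes

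*Combined protocol and SAP*

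**What the plan says.** Protocol section 5.1.1 makes the main endpoint a relative risk of IHC use per detected metastasis. The SAP (Primary endpoint analysis) compares proportions among detected metastases, states that "adjusted risks were calculated using a log-binomial regression model", and reports "95% confidence intervals (CI) calculated by bootstrapping (n=1,000" resamples). Starting values follow a cited approach. Metastasis size and histologic subtype are named as potential confounders.

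The SAP gives no explicit covariate list and no type of bootstrap interval. It has no rule for an arm without events or for resamples with an infinite estimate. One listed reference has separation and infinite estimates in its title, but it is cited only for starting values.

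The design rests on this sentence in protocol section 3.4: "We presume that the AI-algorithm will detect all metastases for which currently IHC is used". The AI-arm proportion over all specimens follows as "P2 = (68-14)/83 = 0.651", where the 14 are all the pilot metastases that needed IHC. The same section reports "All 8 macro-metastases were detected without IHC" and "None of the 8 cases with isolated tumor cells were detected without IHC". The SAP (Sample size calculations) repeats the assumption, admits that it is uncertain, and responds by raising the number to 90 per arm.

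**The concern.** Over all specimens the assumed AI-arm proportion is 0.651, which poses no difficulty. Among detected metastases, the set in which the primary RR is defined, the same assumption is a proportion of 0. A log link cannot represent a zero risk with a finite coefficient, and a bootstrap cannot create events that the sample lacks.

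The RR and its interval are the headline result. An interval of [0, 0] would say that no residual IHC use is compatible with about 26 positives, which so few cases cannot show. The interval gets worse as the intervention gets better.

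**Working it through.** **Inputs.** From protocol 3.4: 68/83 specimens with IHC; 24/83 positive; IHC in 0/8 macro-metastases, 6/8 micro-metastases and 8/8 isolated tumor cells (ITC); 90 per arm. From the SAP: 1,000 resamples. Assumed here: percentile limits, and for the simulation one third of positives in each size class and a common RR.

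**1. The plan's own figure.** With p1 = 68/83, p2 = 54/83 and mean 0.7349, one-sided 5%, power 80%:

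n = [1.645·√(2·0.7349·0.2651) + 0.842·√(0.1481 + 0.2273)]² / 0.1687² = 83.61 per arm.

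This agrees with the protocol. Power at 90 per arm is 82.5%.

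**2. Expected primary table.** Positives per arm: 90 × 24/83 = 26.0. Control positives with IHC: 90 × 14/83 = 15.2. AI-arm positives with IHC: 0. The table is about 0/26 against 15/26.

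**3. The estimate.** With no AI-arm event the likelihood keeps rising as the arm coefficient falls, so log RR is minus infinity and RR = 0. Fits of arm plus size from three sets of starting values all stopped near −23 with a standard error of about 2×10⁴. Better starting values do not help. Robust Poisson, the alternative in protocol 6.1, has the same infinite arm coefficient.

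**4. The interval.** Every resample of AI-arm cases without events has no events, so all 1,000 replicates give RR 0 and the limits are [0, 0]. This does not depend on the covariates.

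**5. What 0/26 against 15/26 supports.** The crude Miettinen-Nurminen score interval runs from 0 to 0.23, and the crude likelihood-ratio interval from 0 to 0.13. A score interval stratified by micro-metastasis and ITC, for 0/9 vs 7/9 and 0/9 vs 9/9, has an upper limit of 0.21.

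**6. Nearly perfect AI.** With control risks of 0, 0.75 and 1, and 26/3 = 8.67 cases per class, P(no AI-arm event) = (1 − 0.75·RR)^8.67 × (1 − RR)^8.67. At RR 0.05 this is 0.9625^8.67 × 0.95^8.67 = 0.46. The other columns come from 1,000 simulated trials with 1,000 resamples each.

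| True RR | No AI-arm event (formula) | Interval [0, 0] | Lower limit 0 | Coverage |
|---|---|---|---|---|
| 0.02 | 74% | 73% | 100% | 27% |
| 0.05 | 46% | 48% | 99.8% | 52% |
| 0.10 | 20% | 20% | 92% | 80% |
| 0.20 | 3.5% | 3% | 65% | 93% |
| 0.30 | 0.5% | 0.6% | 31% | 92% |
| 0.50 | <0.1% | 0% | 2% | 95% |
| 0.70 | <0.1% | 0% | 0.2% | 94% |

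At 0.05 and 0.10 the share of intervals lying below the true RR (48.2% and 19.8%) equals the share of [0, 0] intervals, so almost the whole shortfall comes from these. A smaller run of 300 trials gave coverage of 55% and 80% at 0.05 and 0.10. At 0.20 it gave 90%, but with 7% zero-event trials against 3.5% by formula, so I do not rely on it there.

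**7. A few events.** With k AI-arm events among 26, a resample has none with probability (1 − k/26)^26: 36%, 12%, 4.1% and 1.3% for k = 1, 2, 3 and 4. Up to three events, more than 2.5% of replicates are 0, so the lower percentile limit is 0.

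**8. The empty macro cell.** Take control 6/8 micro and 9/9 ITC, AI arm 1/8 and 2/9. The arm log RR is −1.601 (RR 0.20) with or without an event-free macro stratum. Only the macro coefficient is infinite. The control ITC risk sits at the boundary of 1 here too, and the arm RR stays finite.

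**The case against.** The strongest reply is that perfect detection is a sample-size presumption which the SAP itself calls uncertain, and that the documents report no observed counts. With a true RR of 0.20 or more the planned interval is nearly adequate, and a printed [0, 0] is visibly degenerate. That stands as a limit on the size of the problem. It does not remove it, because a primary interval should work in the scenario for which the trial was sized.

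The test also survives. Protocol 6.1 plans a chi-squared test and the SAP allows Fisher's exact test. For 0/26 against 15/26 Fisher's p is about 3×10⁻⁶. A reader might infer that the significance decision fails; it does not.

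A reader might also blame the inclusion of metastasis size, given the pilot's 0% in macro-metastases. Step 8 shows that this cell is a nuisance and leaves the arm RR unchanged.

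Finally, a reader might conclude that the log-binomial model should be replaced outright. The documents do not support that. Assignment is by two-week period without randomisation, histologic subtype is an a-priori confounder, and the endpoint is an RR, so an adjusted RR model is a reasonable primary estimate.

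**Conclusion.** The point holds for the interval only. Under the plan's own assumption the stated method returns [0, 0], where a score interval reaches about 0.23. That part needs no assumption about covariates.

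The coverage figures (about 52-55% at a true RR of 0.05, 80% at 0.10, 92-93% at 0.20-0.30, nominal from about 0.50) rest on more: percentile limits, 26 positives per arm, the pilot's size mix and control risks, and a common RR. The SAP does not fix the first of these. Nothing in the documents shows that the zero-event case arose in this trial, so no claim about its reported interval follows.

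**What to change.** Keep the adjusted log-binomial RR as planned, and add to the SAP:

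- the covariates and the type of bootstrap interval;
- a switching rule: if the AI arm has no IHC event among detected metastases, or the arm coefficient is not finite in more than 2.5% of resamples, the primary 95% CI for the RR comes from one named method valid with empty cells;
- a statement that an infinite macro-metastasis coefficient alone does not trigger the switch.

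A suitable method is the Miettinen-Nurminen score interval stratified by micro-metastasis and ITC. Used throughout, it covered 95.5% to 96.4% for true RRs from 0.02 to 0.50 in 20,000 simulated trials per RR under the inputs of step 6. A profile-likelihood interval is an alternative. It is narrower here (crude upper limit 0.13), and its coverage was not checked. The choice should be fixed without regard to the data.

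The cost is a few sentences and a few lines of code, plus a wider interval near RR 0. The stratified score interval also leaves out histologic subtype. By steps 6 and 7 the 2.5% trigger acts at up to about three AI-arm events, which is roughly two thirds of trials at RR 0.20, so the adjusted estimate should still be shown beside it. Since the SAP is written in the past tense, for this trial the rule would serve as a check on the reported interval and should be labelled as added later.
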